### **Data analysis**

Data will be analyzed by a statistician based at UWS blind to study group. Analyses of the endpoints will undertake an ‘intention to treat’ approach and compare differences in the primary and secondary endpoints between groups. The primary analysis will compare the proportions of patients with live births. Logistic regression will be used to identify baseline variables which are associated with outcomes. Linear models will be used to test for between group differences in the continuous outcome measures (for example, health status).

Subgroup analyses will be stated *a priori*, for example influence of stimulation doses, long- or short-acting stimulation cycle. Levels of significance will be reported at *P* < 0.05.

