### **Randomization and blinding**

Women will be allocated to a study group by a research nurse phoning the randomization service, prepared and based at the National Health and Medical Research Council Clinical Trials Centre, Sydney, Australia. The randomization sequence is computer generated and concealed via central allocation. There will be stratification by the number of ET cycles (2 to 6 and 6+), woman’s age (<38 years, and 38 to 42 years), and collaborating center. Randomization will be into two study groups, acupuncture and a placebo control using the non-invasive Park needle [18]. Study participants, care providers, the outcome assessors, and the analyst will be blind to study group allocation.

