### **Outcome measures**

Our primary study endpoint will be the proportion of women reporting a live birth defined as the delivery of one or more living infants, >20 weeks gestation or 400 g or more birth weight. Our secondary endpoints will be the proportion of women reporting a clinical pregnancy defined as demonstration of fetal heart activity on ultrasound scan, measured at 7 to 8 weeks, miscarriage defined as a non-viable pregnancy prior to 12 weeks, quality of life using the MOS Short Form 36 (SF36) [19], anxiety using the Stait Trait Anxiety Inventory [20] and infertility self-efficacy measured by the Infertility Self-Efficacy Scale [21] at trial entry, 2 and 14 weeks from trial entry. We will also collect data on expectations, and the therapeutic alliance. Clinical data will be collected from the IVF center database. Other outcomes will be collected by postal questionnaires. Data on the safety of acupuncture and any adverse events will be collected from practitioner treatment notes (Figure 1**)**

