### **Sample size**

Our pilot data [17] were suggestive of a larger treatment difference; however we have chosen a more conservative 7% estimate of the clinical effect from acupuncture compared with the placebo control group. The proportion of women with a live birth for women with multiple cycle failures in the placebo control group in our previous study was 12.1% [17]. To detect a 7% increase in the proportion of women that report a live birth between the treatment and placebo control, with 80% power at the 5% significance level will require 449 women per group. We have allowed for a loss of 30% due to cancelled cycles, or no ET. A total sample size of 1,168 women is required.

We expect a larger treatment effect (10%) when comparing acupuncture and standard care. To detect a 10% increase in the proportion of women that report a live birth between the treatment and standard care, with 80% power at the 5% significance level will require 193 women in the non-randomized group. Allowing for a 30% loss, due to cancelled cycles, or no ET, 251 women in the non-randomized group are required.

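### The primary live-birth comparison names none of the randomization strata; if they are prognostic, an unadjusted test is slightly conservative, and the ET-cycle levels overlap at 6

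*Protocol article*

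**What the plan says.** In the Protocol article, Randomization and blinding, allocation is central and computer generated, with "stratification by the number of ET cycles (2 to 6 and 6" or more), and by age and site: "<38 years, and 38 to 42 years), and collaborating center". The two age levels are exclusive. The two ET-cycle levels share the value 6.

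Outcome measures fixes a binary endpoint: "Our primary study endpoint will be the proportion of women reporting a live birth". Data analysis then states the main comparison in one sentence, "The primary analysis will compare the proportions of patients with live births", and follows it with "Logistic regression will be used to identify baseline variables which are associated with outcomes". No stratification factor is named in either sentence. The word unadjusted is not used, and no specific test is named.

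Sample size uses a simple two-group calculation without strata. The only explicit plan for adjustment is in the opening of Methods/design, and it concerns the non-randomized usual-care group.

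**The concern.** When randomization is stratified on factors that predict the outcome, the arms are balanced on those factors by design. The true sampling variance of the difference between arms is then smaller than the usual two-proportion formula assumes. A test that leaves the strata out uses too large a standard error, so it rejects too rarely under the null and gives up some power under the alternative. The loss costs nothing to recover, because the factors are known for every woman at randomization.

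Two related matters appear in the same passages. The only model named is described as a means of finding associated baseline variables, so its relation to the treatment effect is unclear. And before the ET-cycle factor can enter any adjusted analysis, its levels must be exclusive. Recruitment was under way when the article was written (Trial Status), so the boundary is already in use.

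**Working it through.** **Inputs from the Protocol article (Sample size).** Control rate 12.1% ("in the placebo control group in our previous study was 12.1" per cent); difference 7 points, so 19.1% under acupuncture ("To detect a 7% increase in the proportion of women that report a live birth between the treatment and placebo control"); 80% power; 5% significance; 449 per group; 30% loss; 1,168 in total.

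**The plan's own figure.** Write p0 = 0.121, p1 = 0.191, d = 0.07 and mean p = 0.156.

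- n = [1.96·√(2·0.156·0.844) + 0.842·√(0.121·0.879 + 0.191·0.809)]² / 0.07² = 420.6, that is 421.
- With continuity correction: (420.6/4)·[1 + √(1 + 4/(420.6·0.07))]² = 448.7, that is 449. This matches exactly (two-sided).
- 449 × 1.3 = 583.7, that is 584 per group and 1,168 in total. This also matches.

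The calculation contains no strata, which agrees with reading the primary test as a plain comparison of two proportions.

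**Check 1: formula, one two-level factor.** The live birth rates by stratum are assumptions; the article gives none. For two equal strata with rates a and b and mean m, R² = ((a − b)/2)² / (m(1 − m)). Put k = √(1 − R²). The true standard error is k times the one that the unadjusted test uses, so

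- actual type I error = 2·[1 − Φ(1.96/k)];
- unadjusted power = Φ[(d − 1.96·s0)/(s1·k)];
- adjusted power = Φ[(d/k − 1.96·s0)/s1].

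Here s0 and s1 are the standard errors of the difference under null and alternative. With 409 per arm (1,168 × 0.7 / 2 = 408.8), s0 = √(2·0.156·0.844/409) = 0.02537 and s1 = √((0.121·0.879 + 0.191·0.809)/409) = 0.02526.

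| Assumed rates | R² | Actual type I error | Power, unadjusted | Power, adjusted | Gain (points) |
|---|---|---|---|---|---|
| 20% v 10% | 0.0025/0.1275 = 0.0196 | 4.8% | 79.1% | 79.7% | 0.6 |
| 20% v 7% | 0.004225/0.116775 = 0.0362 | 4.6% | 79.3% | 80.3% | 1.0 |
| 25% v 5% | 0.01/0.1275 = 0.0784 | 4.1% | 79.8% | 82.1% | 2.2 |

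Gains are taken before rounding.

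**Check 2: simulation, all three factors.** Balanced allocation within 2 age × 2 cycle × 4 center strata, 896 women, 12.1% v 19.1%. An unadjusted z test was compared with a stratified Cochran-Mantel-Haenszel (CMH) test, using 100,000 null and 40,000 alternative replicates. Assumed, not in the article: four equal centers, half the women aged 38 or over, 20% in the upper cycle stratum, perfect balance within strata, and the prognostic strengths below (odds ratio for age, odds ratio for cycles, SD of center log-odds).

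| Strength | Type I error, unadjusted | Type I error, CMH | Power, unadjusted | Power, CMH | SE of risk difference, unadjusted v stratified |
|---|---|---|---|---|---|
| None (1, 1, 0) | 0.050 | 0.050 | 82.6% | 82.5% | 0.0241 v 0.0241 |
| Weak (0.7, 0.8, 0.1) | 0.050 | 0.050 | 82.7% | 82.8% | 0.0241 v 0.0241 |
| Moderate (0.5, 0.7, 0.2) | 0.049 | 0.051 | 83.4% | 83.8% | 0.0241 v 0.0239 |
| Strong (0.33, 0.5, 0.4) | 0.045 | 0.051 | 83.7% | 85.1% | 0.0241 v 0.0234 |
| Very strong (0.25, 0.4, 0.6) | 0.040 | 0.050 | 84.1% | 86.6% | 0.0241 v 0.0228 |

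The two checks agree. The loss is nil when the factors carry no information and reaches 86.6 − 84.1 = 2.5 points of power in the extreme case, where the unadjusted standard error is about 5% too large.

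**The overlap.** A woman with 6 earlier transfers satisfies both 2 to 6 and 6+. This needs no calculation.

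**The case against.** The strongest reply is that the criticism rests on silence. A stratified test or an adjusted risk difference also compares proportions, the article does not exclude either, and a condensed article may leave covariates to the full protocol or analysis plan, which are not shown. That stands in part: a reader might infer that the primary analysis definitely ignores the strata, and the text does not establish this. But the main comparison, the sample size formula and the stated use of regression all point to an unadjusted test, and adjustment is mentioned only where the usual-care group is discussed. Naming the strata is therefore a concrete improvement to what is written, not a demand for missing detail.

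The reply continues that the effect is immaterial and conservative. Its size is indeed nil to small. A reader might also call the confidence interval and p-value miscalibrated; the calculations support only somewhat conservative.

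Three further inferences go beyond the documents:

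- That the factors were chosen because they predict live birth. The article gives no reason for the choice.
- That regression will choose covariates for the treatment effect. The article states no selection procedure and describes no adjusted treatment effect.
- That the overlap at 6 contributes to the conservatism, or left women without a stratum. It does not affect the standard error argument, and a central computer-generated system must place each woman somewhere. What is undefined is the published description.

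Finally, the power just below 80% in the first table should not be blamed on the analysis model. It arises because the 30% loss was applied as 449 × 1.3, which leaves about 409 per group. With 449 per group, simulated unadjusted power was at least 82.6% throughout.

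**Conclusion.** The point holds in a limited form. As written, the primary comparison mentions none of the three stratification factors. If they are prognostic, an unadjusted test is slightly conservative and slightly less precise: actual type I error about 4% to 5% against a nominal 5%, and power lower by about 0 to 2.5 points (about 0.4 at the moderate strength simulated and 1.4 at the strong). These figures depend on assumed stratum differences, because the article reports no live birth rates by age, cycle count or center. The treatment estimate remains valid, and the false-positive rate is not raised. The overlap in the ET-cycle levels is a definite wording error, separate from this, which matters here because any adjusted analysis has to use that factor.

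**What to change.** 1. Pre-specify the primary treatment comparison as a logistic regression of live birth on treatment, with age stratum, ET-cycle stratum and center as fixed covariates (small centers pooled by a rule set in advance). Report the odds ratio and the standardized risk difference, each with a 95% confidence interval. The risk difference keeps the result on the scale of the 7-point target. Keep the unadjusted comparison as supportive. If the full analysis plan already does this, say so in the text.
2. Label the regression search for predictors exploratory, and state that it plays no part in choosing covariates for the treatment effect.
3. Check with the randomization service which cut was programmed, restate the ET-cycle levels as mutually exclusive (2 to 5 and 6+, or 2 to 6 and 7+, whichever was used), and use the same cut in the adjusted analysis.

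The cost is a change of wording in the analysis plan and one query to the randomization service. No additional data or participants are needed.

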### **Qualitative study**

A qualitative study using in-depth interviews is nested within the RCT. The purpose of the interviews is: to investigate how women perceive the study intervention and how they think about their use and experience of it, and its effects; and to provide evidence of the process by which the outcomes of the RCT may have been achieved. A sample of 50 women will be recruited through theoretical and purposive sampling to ensure equal numbers of participants from both the intervention and placebo control groups, and a socially diverse sample of women across demographic background, treatment outcome and coping outcomes (as determined by the self-efficacy scores). It is anticipated that 50 interviews will lead to data saturation. The interview will cover topics such as the women’s experience of IVF treatment and its impact on personal wellbeing and social and family relationships, and women’s perception of the impact of acupuncture. Interviews will examine their experience during the period following ET and the pregnancy test. Their beliefs about the impact of acupuncture on their bodies and health, and its potential impact on the reproductive outcome of their treatment will be explored in conversation. Analysis of qualitative interview data will be iterative and the interview schedule will be modified to include emerging themes.

### **Economic analysis**

An economic analysis will be conducted alongside the RCT. The primary measure of outcome for the economic analysis will be the cost per live birth. Resource use collected within the study will include costs associated with the provision of the proposed acupuncture intervention plus the direct costs of IVF based on expected average clinic fees, the frequency and duration of GP visits, the frequency and duration of antenatal visits and inpatient admissions, for example miscarriage loss or antenatal complications. Mean costs and effectiveness between the intervention and control groups will be compared and incremental cost-effectiveness ratios (ICERs) presented in terms of the cost per unit improvement in clinical outcome as measured by the live birth rate. An assessment of the sensitivity of the results obtained to variation in measured resource use, effectiveness and/or unit costs will be undertaken using appropriate one-way and multi-way sensitivity analysis [22]. Data will be collected from Medicare, a national database of health utilization, activity and resource use, and completion of data forms by women reporting health utilization not captured by Medicare.

### **Ethics**

Approval to conduct this study has been obtained from the following research and ethics committees: University of Western Sydney (New South Wales), Greenslopes Private Hospital (Brisbane, Queensland), IVF Australia (Sydney, New South Wales), St Andrews Hospital (Adelaide, South Australia), and the Southern Adelaide Clinical Human Research Ethics Committee (South Australia).

## **Discussion**

IVF is a costly treatment option for women, their partners and the public, and there is a significant personal cost to couples undergoing repeated IVF cycles. Therefore new therapies that improve reproductive and health outcomes are highly desirable. Acupuncture is an emerging therapy used as an adjunct to IVF, and it is important to healthcare consumers and healthcare providers that the evidence base for this modality be established.

This research will add significant new knowledge to defining the role of certain acupuncture protocols applied on the day of ET and one other day of the IVF from a clinical and cost-effectiveness perspective. The study design utilizing mixed methods will also generate a different form of new knowledge that will allow the social and personal experience of acupuncture to be explained and their relationship to acupuncture determined. The research will add significantly to the clinical evidence base to allow conclusions to be made on the role of acupuncture to improve reproductive outcomes.

### **Trial Status**

This trial is currently recruiting participants.
